## Introduction

Irritable bowel syndrome (IBS) is characterized by abdominal pain, bloating and changes in bowel habit, in the absence of an identifiable organic disease . This functional disorder is very common as its prevalence is estimated around 10%-15% in Europe and the United States . IBS chronicity severely impacts patients' quality of life and generates large healthcare costs . The high prevalence and the absence of effective treatments make this disease a public health concern. The mechanisms involved in visceral pain and IBS symptoms are still unknown. Recent studies indicate that alterations of the intestinal epithelial barrier is a key pathophysiological event in IBS, allowing maintenance of a low grade mucosal inflammatory state, leading to visceral hypersensitivity (VH) and pain . This VH, highlighted by the colorectal distension test , is found in more than half of IBS patients . Hypersensitivity implies sensitization of somatic or visceral primary afferent fibres, involving an increase in excitability. In several animal models of chronic pain, this hyperexcitability has been linked to a remodelling of ion channel expression patterns . Several voltage-gated ion channels are involved in neuronal firing, including T-type calcium channels, especially Cav3.2 member . We recently found in a case-control study that this Cav3.2 channel was overexpressed in the colonic mucosa of IBS patients compared to asymptomatic controls . Moreover, it has been shown that the blockade of Cav3.2 channels, in an animal model mimicking IBS, prevented the development of colonic hypersensitivity . We aimed to evaluate the efficacy and the safety of a T-type calcium channel blocker –ethosuximide– in the treatment of abdominal pain in IBS patients.

### T-type calcium channels, ethosuximide and IBS:

For ten years, Cav3.2 channels have been extensively studied and shown as involved in nociceptive pain . Marger *et al.* recently demonstrated, in an animal model of butyrate-induced VH, that Cav3.2 channels were involved in chronic visceral pain . They have shown that Cav3.2 channels were overexpressed in the dorsal root ganglion neurons innervating the colon and that their pharmacological blockade prevented the development of colonic hypersensitivity. Recently, we demonstrated in a case-control clinical study, that Cav3.2 channels were overexpressed in the colonic mucosa of IBS patients compared to asymptomatic controls . These channels are located particularly in peripheral nerve fibres, supporting their involvement in the development of colonic hypersensitivity. Cav3.2 channels appear to be an interesting pharmacological target to treat visceral pain related to IBS. The therapeutic effect of ethosuximide was studied in several animal models of chronic pain: traumatic neuropathy  and chemotherapy-induced peripheral neuropathy , inflammatory  and acute pain . Moreover, ethosuximide was shown to be a modulator of pro-nociceptive effects of hydrogen sulfide (H2S) , a gazotransmitter involved in VH related to IBS  and a Cav3.2 channel activator . Thus, according to the results of these studies, ethosuximide, by its action on T-type calcium channels, seems to be a promising and innovative therapeutic in the treatment of abdominal pain in IBS patients.

### Summary of hypotheses and objectives:

T-type calcium channels blockers have a major interest for the development of new symptomatic treatment of pain related to IBS. There is an opportunity to conduct an innovative proof-of-concept trial in IBS patients with such a blocker, ethosuximide, which is currently available on the European market (to

treat epilepsy). The demonstration of clinical efficacy would enrich our pharmacopoeia to treat pain related to IBS.

The primary objective of this study is to evaluate the efficacy of ethosuximide versus placebo, administered in addition to background therapy, on intensity of abdominal pain related to IBS and to evaluate the score of the Subject Global Assessment (SGA scale) of Relief.

The secondary objectives concern the effects of ethosuximide on:

- the severity of IBS symptoms,
- the quality of life (physical and mental),
- the safety of ethosuximide.

The study discontinuation rate and analgesics and transit regulator consumption will be assessed throughout the study.

#### Trial design:

Multicentre, randomized, double-blind, parallel group and controlled pilot clinical trial.  
Safety and efficacy.

## **Methods**

Study setting: Academic Hospitals

#### Eligibility criteria:

##### *Inclusion criteria*

- Man or woman aged 18 or more.
- Negative pregnancy test and effective contraception.
- IBS defined by ROME IV criteria.
- Treatment failure (11-points NRS abdominal pain  $\geq 4$ ) for at least 3 months despite stable treatment for a month.
- Patients affiliated to the regime of the French Social Security.
- Patients able to deliver a free and informed consent.

##### *Exclusion criteria*

- Breastfeeding.
- Diabetic patients.
- Chronic pain of greater intensity than the pain related to IBS.
- Renal or hepatic impairment defined by significant liver function (liver enzymes  $> 3 \times$  normal values, cholestasis) and renal (MDRD  $< 60$  ml/min) abnormalities.
- History of severe or current depression (hospitalization, long-term antidepressant treatment).
- Addiction to alcohol and/or drugs.
- Patient already treated with antiepileptic.
- Allergy to succinimide (ethosuximide, methsuximide, phensuximide).
- Psychotic disorders.
- Insufficient cooperation and understanding to adhere strictly to the conditions provided by the study.
- Patients undergoing a measure of legal protection.

### Interventions:

Study methodology was selected on the recommendation of the European Medicines Agency (ICH guideline Irritable Bowel Syndrome: EMA/CHMP/60337/2013-CPMP/EWP/785/97 Rev. 1; for short treatment on all types of IBS).

Patients will be treated for 12 weeks either by ethosuximide or a placebo, according to a regimen with a specific titration.

### *Enrolment*

Patients followed in their referral centre for the treatment of IBS will be pre-selected. Patients will be contacted in order to briefly present the purpose of the study and make an appointment for the inclusion visit.

### *Visit 1 - Inclusion (D0-7) and run-in period (D0-7 to D0)*

The objectives of the study, practice organisation, and constraints will be explained in details. The investigator will present the information and consent form. The patient must present an IBS diagnostic defined according to the ROME IV criteria. Two blood samples will be taken (blood count, hepatic enzymes, renal function,  $\beta$ -HCG and genetic analysis).

A daily logbook will be given to the patient with detailed explanations to collect daily, every week before planned visits, the median abdominal pain score experienced during the last 24 hours and the Bristol score. Side effects should be collected. The patient will return home with a logbook for 7 days, corresponding to the run-in period. This run-in period, without any studied treatment, was introduced (i) to evaluate the ability of the patients to rate their abdominal pain daily in their logbook; (ii) to check the basal average pain intensity over a 1-week period. The patients received the treatment after this run-in period only if the inclusion criteria were met (11-points NRS abdominal pain  $\geq 4$  and completed logbook as required by the protocol).

### *Visit 2 - Start treatment (D0)*

Daily average abdominal pain scores have to be filled-in by the patient on the logbook during the last 7 days and the average abdominal pain score should be  $\geq 4$  to include the patient in the study. The patients have to fill-in three questionnaires: 1) IBS-SSS, 2) EQ-5D and 3) GIQLI.

If all the inclusion and non-inclusion criteria are conformed, the patient will be enrolled in the study and randomised in one of the two treatment arms (ethosuximide or placebo). The administration dosages, according to a specific titration regimen, will be explained in details to the patient. At the end of the visit, the patient will receive all the therapeutic units for the duration of administration required by the study protocol (4 weeks) and the daily logbook.

### *Treatment period 1 - Dose escalation - (D0 to D0+4 weeks)*

Ethosuximide or placebo treatment will be administered daily during dinner, according to a regimen of specific titration for 28 days (maximum dose of 10 ml/day). The patient will assess and record the following daily in the logbook:

- The evening before bed: abdominal pain felt in the last 24 hours with the 11-points NRS,
- The evening before bed: the number, shape and consistency of the stool with the Bristol's scale,
- Side effects or any other particular event should also be carefully noted in the daily logbook,
- Treatment modification.

Every 7 days (at the end of each dose escalation level), patients will be contacted by phone call by investigator in order to collect information on any side effects and inform the patient of the increased dose

in case of inefficiency and good tolerance. Stopping or decrease dosage will be used in cases of intolerance or effectiveness of the treatment.

#### *Visit 3 – follow-up visit (D0+4 weeks)*

This first visit will provide information on the therapeutic dose with an optimal benefit-risk ratio for the patient.

During the visit, the patient will complete questionnaires IBS-SSS, EQ-5D, GIQLI questionnaires and the SGA scale. At the end of the visit, the patient will receive all therapeutic units for the next treatment period prescribed by the protocol (4 weeks) and the logbook.

#### *Treatment period 2 and 3 (D0+4 weeks to D0+8 weeks and D0+8 weeks to D0+12 weeks)*

Likewise treatment period 1. To note that the patient will assess and record, only the 7 days before the next visit, the following in the logbook:

- The evening before bed: abdominal pain felt in the last 24 hours with the 11-points NRS,
- The evening before bed: the number, shape and consistency of the stool with the Bristol's scale.

#### *Visit 4 and 5 – follow-up visit (D0+8 weeks and D0+12 weeks)*

Likewise visit 3. Visit 5 closing the treatment period.

To note that at the end of visit 5, will be given to the patient the abdominal pain 11-points NRS to complete daily for 7 days, 3 weeks after the visit 5 ( $\pm 1$  week).

#### *Phone call follow-up to D0+15 weeks ( $\pm 1$ week)*

This phone call aims to recover daily scores of abdominal pain during the last 7 days. This phone call closes the patient's study participation.

- All patients followed the same procedures (assessment of pain, filling questionnaires and taking treatment in the indicated dosage level).
- No deviation to the protocol will be allowed during the entire study.
- To verify patient compliance, accounting treatment units will be made at each planned visits.
- No change of treatment will be allowed during the test.

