#### Genetic analysis of cytochromes P450:

A blood sampling (1 tube of 6 ml) will be performed for the genetic analysis of the genes coding for CYP3A4 and CYP2E1, involved in the metabolism of ethosuximide. This genetic analysis will make it possible to demonstrate the existence (or not) of slow / fast metabolizers in our studied population. The demonstration of slow / rapid metabolizers will enable us to carry out a more precise analysis on the therapeutic efficacy of ethosuximide.

These blood samples will be strictly used in this study and a specific document informing the patient and obtaining his authorization will be provided during the first visit (D0-7).

Analgesic and antispasmodic/regulators transit consumption: Drugs consumption for IBS will be evaluated throughout the study

Safety: Any adverse events were collected daily by the patient and during the planned phone calls by investigators (every 7 days). Adverse events are categorized according to their type, intensity and treatment related by investigators. Due to the long half-life of ethosuximide (60h), a phone call, within 3 weeks after stopping treatment, will be allowed to recover any adverse effects.

Study discontinuation rate will be evaluated and compared in the two treatment arms.

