#### Data collection, management, and analysis:

##### *Data collection methods*

Data entry will be made by the investigators and CRA of each clinical centre, at each planned visits and during the ambulatory period.

Data entry will be centralized in the coordinating centre (CHU Clermont-Ferrand), from an electronic case report form (e-CRF, Ennov Clinical, France) filled-in during site visits.

All patients will be analysed (intent to treat analysis). However, if a major deviation from the protocol (non-respect of co-occurring treatment, inclusion / exclusion criteria and the study design) only safety data will be evaluated.

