### 1.2 Secondary objectives

The secondary objectives concern the effects of ethosuximide on:

- ▶ the severity of IBS symptoms
- ▶ the quality of life (physical and mental)
- ▶ the safety of ethosuximide.

The study discontinuation rate and analgesics and transit regulator consumption were assessed throughout the study.

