### 1.9 Secondary outcome measures

Secondary outcome measures include:

- The quality of life was evaluated by the GQLI and EQ-5D-3L (EuroQol group), which assess the physical and mental health of IBS patient.
- The severity of IBS symptoms was evaluated by IBS-SSS questionnaire and Bristol scale.
- The safety of ethosuximide was evaluated by daily collection of adverse effect by patient.
- Analgesic consumption throughout the study.

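### Limiting patients who change IBS co-medication to safety data is a post-randomisation exclusion that contradicts the plan's own intention-to-treat and non-responder rules and weakens the drug-consumption outcome

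*Combined protocol and SAP*

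**What the plan says.** **Consumption as an outcome.** The protocol's summary of objectives states that "analgesics and transit regulator consumption will be assessed throughout the study". The consumption paragraph, which sits under the cytochrome P450 heading, says "Drugs consumption for IBS will be evaluated throughout the study". SAP 1.2 repeats the objective: "The study discontinuation rate and analgesics and transit regulator consumption were assessed throughout the study". The outcome list in SAP 1.9 is narrower: "Analgesic consumption throughout the study", with no transit regulators.

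**Changing treatment.** The general rules at the end of the protocol's phone-call follow-up section say "No change of treatment will be allowed during the test". Data collection methods then says that "if a major deviation from the protocol (non-respect of co-occurring treatment, inclusion / exclusion criteria and the study design) only safety data" will be evaluated.

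**Who is analysed.** The sentence before that one in Data collection methods commits to analysing all patients by intention to treat. Statistical methods lists ITT, mITT and per-protocol analyses and scores non-compliant patients as non-responders. SAP 2.1 names the same three sets. SAP 2.2 then says the ITT population will not be analysed, and removes from both mITT and per-protocol any patient with a major deviation, explained only as a missing primary outcome or non-compliance.

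**What is recorded.** At Visit 1 the logbook collects "the median abdominal pain score experienced during the last 24 hours and the Bristol score", plus side effects. Treatment period 1 adds a treatment-modification item. Treatment periods 2 and 3 are said to follow period 1, but with this restriction: "To note that the patient will assess and record, only the 7 days before the next visit, the following in the logbook". The list that follows holds pain and stool only.

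**The endpoint.** The responder definition (protocol Primary endpoint, SAP 1.8) has no condition on added analgesics or antispasmodics. The only analgesic variable in the models is use at inclusion, yes or no (SAP 2.4).

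**The concern.** A change in analgesic or transit drug after randomisation is not a neutral administrative event. Patients whose pain persists may add a drug, and patients who improve may drop one. If the trial drug works, both happen at rates that can differ between arms. Removing these patients from efficacy therefore conditions the comparison on something treatment can affect, and randomisation no longer protects it.

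The same rule reaches the consumption outcome, which the protocol lists separately from safety. The patients confined to safety data are those whose drug use changed, so those left carry much less of the information the outcome was meant to give.

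The 10% allowance in the sample size is stated for loss to follow-up only, so it makes no provision for these removals.

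**Working it through.** **1. Do the rules agree on a patient who changes IBS co-medication?**

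| Place | Handling |
|---|---|
| Protocol, Data collection methods, ITT sentence | Kept |
| Same section, next sentence | Safety data only |
| Protocol, Statistical methods | Non-responder, if the change counts as non-compliance |
| SAP 2.2, ITT | Set defined but not analysed |
| SAP 2.2, mITT and per-protocol | Removed, if the change counts as non-compliance or a major deviation |

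Non-compliance is not defined. The only text that says whether a co-medication change is a major deviation is the protocol sentence, and it says yes. No set that the SAP will analyse clearly keeps these patients.

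**2. The plan's own figure.** Inputs (protocol Sample size, SAP 1.7): 35% v 55%, two-sided 5%, 90% power, 130 per arm, 10% loss.

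- Power = Φ[(d − 1.96·se0)/se1], where se0 uses the pooled rate and se1 the separate rates.
- se0 = √(0.45 × 0.55 × 2/130) = 0.0617; se1 = √((0.35 × 0.65 + 0.55 × 0.45)/130) = 0.0604.
- (0.20 − 1.96 × 0.0617)/0.0604 = 1.31, so power is 90.5%.
- The formula needs 128 per arm for 90%, and 130/0.9 = 144.4, rounded up to 145. The stated 130 and 145 reproduce.

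**3. Effect of removal.** The documents give no rate of co-medication change, so the rates below are assumptions. Let r be the share removed in an arm and p its planned rate. The remaining number is 130(1 − r).

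- All removed are non-responders: the observed rate is p/(1 − r).
- All removed are responders: the observed rate is (p − r)/(1 − r).

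| Assumed removal (placebo, ethosuximide) | Observed rates | Difference | Risk ratio | Power |
|---|---|---|---|---|
| None | 35% v 55% | 20.0 | 1.57 | 90.5% |
| Non-responders, 20% and 10% | 43.75% v 61.1% | 17.4 | 1.40 | 74% |
| Non-responders, 10% and 10% | 38.9% v 61.1% | 22.2 | 1.57 | 93% |
| Responders, 10% and 20% | 27.8% v 43.75% | 16.0 | 1.58 | 70% |
| Responders, 10% and 10% | 27.8% v 50.0% | 22.2 | 1.80 | 94% |

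Second row: 0.35/0.80 = 0.4375 on 104 patients and 0.55/0.90 = 0.6111 on 117. The difference is 0.1736, with se0 = 0.0673 and se1 = 0.0663, giving Φ(0.63) = 74%.

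Removal unrelated to outcome costs only precision: a further 10% or 20% of the 130 per arm gives 87% or 83% power.

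**4. If the patients are kept with no rule on added drugs.** Assume that half of those who add a drug become responders through it. With 20% adding on placebo and 10% on ethosuximide, the rates are 0.35 + 0.10 = 45% and 0.55 + 0.05 = 60%: 15 points, 68% power. With 10% in each arm they are 40% and 60%: 20 points, 90% power.

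**The case against.** Much can be said for the plan.

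- **Wording.** Consumption is to be assessed or evaluated; only the discontinuation rate is to be compared between arms. As-needed intake can vary under an unchanged prescription, and drug use can be described in every randomised patient. A reader might infer that the consumption objective cannot be answered at all. The documents do not support that. This point stands.
- **Data.** Treatment period 1 logs treatment modifications, periods 2 and 3 are said to follow it, and use at inclusion gives a coarse baseline. The eCRF and logbook templates are not in the documents, so a complete absence of drug-intake data is not established. What remains is that the explicit lists for the run-in and the 7-day windows do not name drug intake.
- **The ban.** The word treatment in the follow-up section is ambiguous. Read as study drug, it clashes with the titration in treatment period 1; read as background drug, it fits better, but that is inference. The point therefore rests on Data collection methods.
- **Removal is not settled.** The ITT sentence and the non-responder rule point the other way, and SAP 2.2 does not name co-medication. True, but this is the contradiction itself. It also means that removal and unadjusted retention are alternatives, not two faults in the same patient.
- **Direction.** A reader might infer that every handling shrinks the treatment difference. The equal-rate rows show otherwise. Direction and size come from the assumed inputs.
- **Retention.** Counting patients regardless of co-medication is a recognised treatment-policy strategy and not an error in itself. The gap is that the plan does not say it has chosen it.

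**Conclusion.** The concern holds as an unresolved contradiction with a real risk of bias. The protocol's safety-only rule for co-medication changes conflicts with its own ITT sentence and with its non-responder rule. The SAP does not rescue these patients, because it sets ITT aside and leaves non-compliance undefined in both remaining sets.

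The bias can go either way. In the removal scenarios shown, the planned 20 points becomes anything from 16.0 to 22.2, and power runs from 70% to 94% against 90.5%. These figures rest on assumed removal rates of 10% to 20% and on the extreme assumption that all those removed share one outcome. They show sensitivity and are not forecasts.

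The consumption outcome is compromised and loosely defined, not impossible. The SAP treats secondary endpoints as exploratory, so the larger stake is the primary comparison.

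**What to change.** 1. In the protocol's Data collection methods, remove the co-medication item from the deviations that limit a patient to safety data. In SAP 2.2, state that a change in IBS co-medication is not a reason for exclusion from the primary analysis set. Keep these patients in the primary and consumption analyses.
2. Add a supportive analysis of the primary endpoint that scores patients with new or increased IBS co-medication as non-responders, in line with Statistical methods. Define in advance what counts as an increase, so that trivial variation in as-needed use does not override a response.
3. Carry the treatment-modification logbook item, with drug name and quantity, explicitly into the run-in week and the 7-day windows of treatment periods 2 and 3. Restore transit regulators in SAP 1.9 to match SAP 1.2.
4. The sponsor must reconcile treatment period 1, the follow-up section's general rules, the consumption paragraph and Data collection methods on which co-medication changes are allowed. No clinical rule is proposed here.

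The cost is a slightly longer diary entry, short wording changes in both documents and one extra analysis. The supportive analysis may show lower responder rates than the main one.

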#### Outcomes:

Study endpoints were selected on the recommendation of the European Medicinal Agency (ICH guideline IBS: EMA/CHMP/60337/2013-CPMP/EWP/785/97 Rev. 1: for short treatment on all types of IBS).

#### *Primary endpoint*

Rate of responders to treatment; a patient will be considered as a responder if he satisfies two conditions: 1) a decrease of at least 30% of the score of abdominal pain (11-points NRS) compared to the score before treatment, and 2) a significant global improvement defined by a score of 4 or 5 on the SGA scale.

Abdominal pain intensity (11-points NRS): This scale allows the patient to rate his abdominal pain from 0 to 10; with 0 is no pain and 10 the worst possible abdominal pain. The intensity of abdominal pain (the past 24 hours) will be measured daily (the evening) by the patient on the logbook, and the values will averaged for the 7 days preceding the two time points D0 (baseline) and D0+12 weeks (last visit). The primary endpoint is the calculated difference  $\Delta(\%) = ((\text{NRS}(\text{D0}) - \text{NRS}(\text{D0+12 weeks})) / \text{NRS}(\text{D0})) \times 100$ .

Subject Global Assessment of Relief: The Subject Global Assessment of Relief  aims to assess the effectiveness of a specific treatment on symptoms of IBS. This scale consists of 5 levels of description answering the question "Please consider how you felt during the past treatment period in regard to your IBS, in particular your overall well-being, and symptoms of abdominal pain/discomfort and altered bowel

habit". Levels of description are declined such as: 1) worse, 2) not at all relieved, 3) somewhat relieved, 4) considerably relieved and 5) completely relieved".

These simple responses sign both satisfaction and dissatisfaction. This evaluation will be conducted during the last visit of the study (D0+12 weeks).

